### Termination and withdrawal criteria

2.9

All participants were informed that they had the right to drop out of the study before starting the experiment. The test will also be withdrawn or terminated if the following criteria occur.

1.Side effects and adverse reactions occur, which are difficult for patients to tolerate.2.Serious adverse events occurred.3.Complicated with other diseases during the test.4.Patients with poor compliance and failed to perform research protocol as required.

### Test drugs

2.10

Test drugs including FBD and placebo were prepared by the Department of Pharmacy of the Affiliated Hospital of Chengdu University of Traditional Chinese Medicine. The composition of the FBD is as follows: Raw Rhubarb (Sheng dahuang) 20 g, Coptidis Rhizoma (Huang lian) 15 g, Fructus Forsythia (Lian qiao) 15 g, Aluminum potassium sulfate (Ku fan) 10 g, Pseudobulbus Cremastrae Seu Pleiones (Shan cigu) 10 g. All herbs are mixed, soaked, cooked, and made into a single-dose pouch of uniform specifications by the pharmacy department, each bag is about 150 mL. Placebos are made from starch without active ingredients and added a variety of food colors. The placebo was consistent with the FBD in color, odor, and dosage. Furthermore, the ordinary dressings and silver ion dressings should also have no difference in appearance and smell.

## Interventions

3

### Treatment plan

3.1

Both groups received based on dietary treatments recommended by the Diabetes UK evidence-based nutrition guidelines for the prevention and management of diabetes,^[29]^ and controlled blood glucose, lowered blood lipids, adjusted blood pressure, and suppressed infections according to individual conditions during the trial period. At the same time, DF ulcers can be treated by surgical debridement to remove necrotic tissue, improve lower limb circulation and a routine dressing every 2 to 3 days according to the Diabetic Foot Ulcer Treatment Guidelines.^[30]^

Experimental group: The participants in experimental group took a foot bath 1 to 2 times a day. Each bag of FBD was dissolved in 300 mL of warm water for 30 minutes, then cover the wound with a ordinary dressing.

Control group: The patients in the control group will be given a placebo decoction for foot bath twice daily for 30 minutes. The immersion method is the same as the experimental group. In contrast, half of the patients covered the wound with an ordinary dressing and half with a silver ion dressing.

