### Sample size

2.4

This study is a superiority clinical trial with interleukin 6 (IL-6) as the main efficacy indicator, so we chose the mean superiority test of 2 independent samples to estimate the sample size. According to the previous relevant references,^[25]^ the optimal response rate was set to 0.04. The mean values of the experimental group and the control group were 6.14 and 6.21, and the combined standard deviation of the 2 groups was 0.14. At the same time, set *a* to 0.025 and *b* to 0.2. Enter the above values into the Power Analysis and Sample Size version 11.0 (PASS 11.0) software to calculate the sample size for the experimental group as 20 and the control group as 40. Finally, the total number of study samples is determined to be 60 cases.

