### Blinding

2.6

The study was a double-blind clinical trial. All researchers, subjects, and statisticians were blinded throughout the intervention period. Unless participants have serious adverse events to receive emergency treatment, they cannot eliminate blindness. Both the FBD and the placebo granules will be produced by the Pharmacy Department of Hospital of Chengdu University of Traditional Chinese Medicine. Both are ensured to be consistent in appearance, shape, or odor and specifications. Moreover, ordinary dressings must also be no different from silver ion dressings in terms of appearance and smell. It is worth mentioning that research members cannot discuss with the participants their possible treatment options.

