### Outcome measures

3.2

Primary efficacy outcomes:

1.IL-6 and tumor necrosis factor α (TNF-α) were detected by enzyme-linked immunosorbent assay and were measured before and each week after treatment during entire treatment.2.Wound pathogen distribution: Collect samples of ulcers and use a fully automatic microbiologic tester for bacterial detection once a week.

Secondary efficacy outcomes:

1.Blood glucose and blood lipid: The blood glucose, total cholesterol, triglyceride, low-density lipoprotein cholesterol, and high-density lipoprotein cholesterol are detected by a fully automatic biochemical analyzer.2.Wound area: Long multiplied by high area. First take a picture of the wound and then read the data with Image J software. The above operations are performed by the same doctor.3.Lower extremity blood vessel diameter, blood flow velocity: detected by lower extremity blood vessel Doppler ultrasound.4.Walking speed, walking distance: Make patients walk on a flat ground with a scale, and calculate the distance and speed.5.TCM syndrome score: Recorded with TCM Syndrome Score Evaluation Form.

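### Foot-bath frequency differs by arm (FBD once or twice a day, placebo twice), which conflicts with the stated blinding and allows 0% to 50% less soaking in the FBD arm

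*Protocol article*

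**What the plan says.** Section 3.1 describes the two regimens in adjacent paragraphs. Experimental arm: "The participants in experimental group took a foot bath 1 to 2 times a day". Control arm: "The patients in the control group will be given a placebo decoction for foot bath twice daily for 30 minutes". The control paragraph adds that immersion is done in the same way as in the experimental arm. No criterion is given for choosing one bath or two.

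Two other sections bear on this. Section 2.6 (Blinding) states: "All researchers, subjects, and statisticians were blinded throughout the intervention period". Section 2.10 (Test drugs) states: "The placebo was consistent with the FBD in color, odor, and dosage". Section 2.4 (Sample size) plans 20 experimental and 40 control patients.

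**The concern.** A placebo bath is there so that the arms differ in the herbs and not in the soaking. That requires the same number of baths in each arm. The article's own rationale makes this relevant: the Introduction says that a foot bath can inhibit bacteria by changing the environment on the ulcer surface, and wound bacteria are among the primary outcomes.

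The second problem is blinding. If one bath a day is allowed in the FBD arm only, staff must know the arm to apply the rule, or must work from arm-specific instructions that reveal it. The consequences would be greatest where judgement or effort enters. Background care is one such place: section 3.1 has patients' clinicians control glucose, lipids and blood pressure, and says they "suppressed infections according to individual conditions during the trial period", with surgical debridement also allowed. The walking tests and the syndrome score ("TCM syndrome score: Recorded with TCM Syndrome Score Evaluation Form") are others. The ELISA measurements of IL-6 and TNF-α and the automated bacterial detection are less exposed to assessor knowledge. Unequal soaking or unequal co-treatment could still reach them.

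**Working it through.** The article states no exposure figure, so there is none to reproduce. The check is arithmetic on the stated rules.

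**Inputs**
- FBD frequency: 1 to 2 baths a day (section 3.1).
- Placebo frequency: 2 baths a day, 30 minutes each (section 3.1).
- FBD bath length: taken as 30 minutes. This is an assumption, because the FBD sentence attaches the 30 minutes to dissolving the bag. The statement that immersion is done in the same way in both arms supports it.
- Planned sizes: 20 FBD, 40 control (section 2.4).

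**Number of baths per week**
- FBD: 7 × 1 = 7 to 7 × 2 = 14.
- Placebo: 7 × 2 = 14.
- Difference: 14 − 14 = 0 to 14 − 7 = 7, that is 0/14 = 0% to 7/14 = 50%. This range needs no assumption about bath length.

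**Soaking time, at 30 minutes a bath**
- FBD: 7 × 0.5 h = 3.5 h to 14 × 0.5 h = 7.0 h a week.
- Placebo: 14 × 0.5 h = 7.0 h a week.
- With an average of f baths a day on FBD, the shortfall is 1 − f/2: 50% at f = 1, 25% at f = 1.5, 0% at f = 2.

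**What a prescribed schedule reveals**

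Let s be the share of FBD patients prescribed one bath a day. The documents do not give s, so it ranges from 0 to 1.
- FBD patients identifiable by their schedule: 20s, that is 0 to 20.
- Probability of FBD before the schedule is known: 20/60 = 33%.
- Given a once-daily prescription: 20s/(20s + 0) = 100% for any s > 0.
- Given a twice-daily prescription: 20(1 − s)/[20(1 − s) + 40], which is 20/60 = 33% at s = 0, 10/50 = 20% at s = 0.5, and 0/40 = 0% at s = 1.

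These probabilities apply to someone who knows the rule, and to the schedule prescribed. They do not apply to baths taken, since a control patient may also miss a bath.

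**Does any other text equalise the frequencies?** The remark about the same immersion method concerns how the soak is done, and it follows directly on a control frequency that differs from the experimental one. The matching in section 2.10 names dosage but gives no number of baths. Neither overrides the explicit frequencies.

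**The case against.** The strongest reply is that this is loose wording in a condensed article. The same-immersion remark, the matched dosage in section 2.10 and the matched specifications in section 2.6 all suggest that equal regimens were meant. The FBD sentence is in the past tense and could describe baths taken, while the placebo sentence prescribes. Twice daily satisfies both statements, so if every FBD patient is told to bathe twice a day, exposure is equal and nothing is revealed. The pharmacy could also print directions on coded pouches, so that staff need not know the arm. Finally, the primary outcomes are laboratory measures, and every figure above runs from no effect to a theoretical maximum.

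Much of this stands. A drafting slip is quite possible, the lower bound is zero, and unblinding is a smaller risk for the laboratory outcomes. The tense argument is weak, because tenses are mixed throughout the article. Pouch labels do not help: a label reading one to two times a day in one arm and twice a day in the other would itself show the arm. What remains is that the text permits once daily in one arm and not in the other, and sites that follow it could apply different schedules.

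**Conclusion.** The concern holds. The mismatch in the text is certain. Its effect is conditional: the FBD arm may have 0% to 50% fewer baths than placebo (0 to 7 fewer a week), and between 0 and 20 of the 20 FBD patients could be identifiable from a once-daily prescription. Both upper limits require every FBD patient to be on one bath a day; both lower limits require none to be. The hours figure (3.5 to 7.0 h against 7.0 h a week) rests in addition on a 30-minute FBD soak.

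The documents do not fix the direction of bias. If soaking itself helps, fewer FBD baths work against FBD; if it harms the wound, they work in its favour. Nothing here shows that unblinding has occurred. It is worth correcting because the schedule as written undermines both the blinding and the purpose of the placebo bath.

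**What to change.** Replace the two frequency statements in section 3.1 with one that applies to every arm, for example: all participants take a 30-minute foot bath twice daily. Twice daily is the only frequency that both present statements allow, but the choice is the investigators'. If frequency may be changed for a patient, write one rule whose criteria do not mention the arm, and apply it in all arms without knowledge of allocation.

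With a common schedule of two 30-minute baths, each arm soaks for 60 minutes a day, the planned difference is 0%, and the schedule no longer tells anyone the arm.

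It would also be useful, though the correction does not depend on it, to record baths prescribed and baths taken in the case report form if this is not already done.

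The cost is one protocol sentence and, at most, one case report form field. Sample size, outcomes and visits do not change.

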### Outcome measures

3.2

Primary efficacy outcomes:

1.IL-6 and tumor necrosis factor α (TNF-α) were detected by enzyme-linked immunosorbent assay and were measured before and each week after treatment during entire treatment.2.Wound pathogen distribution: Collect samples of ulcers and use a fully automatic microbiologic tester for bacterial detection once a week.

Secondary efficacy outcomes:

1.Blood glucose and blood lipid: The blood glucose, total cholesterol, triglyceride, low-density lipoprotein cholesterol, and high-density lipoprotein cholesterol are detected by a fully automatic biochemical analyzer.2.Wound area: Long multiplied by high area. First take a picture of the wound and then read the data with Image J software. The above operations are performed by the same doctor.3.Lower extremity blood vessel diameter, blood flow velocity: detected by lower extremity blood vessel Doppler ultrasound.4.Walking speed, walking distance: Make patients walk on a flat ground with a scale, and calculate the distance and speed.5.TCM syndrome score: Recorded with TCM Syndrome Score Evaluation Form.

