**Methods::**

This study is a multicenter, double-blind, randomized, placebo controlled clinical trial in which 60 eligible participants were randomly divided into an experimental group and control group at a 1:2 ratio. Both groups received the same basic treatment for DF disease, the experimental group used FBD and ordinary dressing changes, while half of the patients in the control group received placebo and ordinary dressings, and the other half received placebo and silver ion dressings. Patients in both groups will be evaluated weekly for efficacy during the intervention. The primary efficacy indicators include the types of wound pathogens, interleukin 6 and tumor necrosis factor α. Secondary efficacy indicators included blood glucose, blood lipids, wound area, lower extremity blood vessel diameter, blood flow speed, walking speed, walking distance, and traditional Chinese medicine syndrome scores. We will also conduct a safety evaluation of the drug at the end of the trial.

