### Statistical analysis

3.5

The data of the study will be analyzed by statistical analysis software packages SPSS 23.0 and will be performed by experts from the Statistics Teaching and Research Office of Chengdu University of Traditional Chinese Medicine. The measurement results was calculated by *t* test, and the results were expressed as “mean ± standard deviation.” Chi-squared test was used to analyze the count data. The paired design *t* test was used for comparison the differences between before and after treatment with the same group, and the independent sample *t* test was used for comparison the differences between groups. The comparison of incidence of adverse events between the 2 groups using Chi-squared test or Fisher exact probability method. If *P* < .05, it was considered as a statistically significant difference.

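### The trial is sized on IL-6 alone but lists three unranked primary outcomes with no deciding visit and one P < .05 rule: up to about 14% false-positive risk at a single visit if any one may carry the claim

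*Protocol article*

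**What the plan says.** - **Sample size (2.4).** The calculation is made "with interleukin 6 (IL-6) as the main efficacy indicator", with alpha 0.025 and beta 0.2, giving 20 experimental and 40 control patients. No visit is named for the IL-6 comparison.
- **Abstract, Methods.** "The primary efficacy indicators include the types of wound pathogens, interleukin 6 and tumor necrosis factor α". It adds: "Patients in both groups will be evaluated weekly for efficacy during the intervention".
- **Outcome measures (3.2).** IL-6 and TNF-α form the first primary item and "were measured before and each week after treatment during entire treatment". Wound pathogen distribution is the second: "Collect samples of ulcers and use a fully automatic microbiologic tester for bacterial detection once a week". None of the three is placed above the others, and no week is singled out.
- **Statistical analysis (3.5).** "the independent sample *t* test was used for comparison the differences between groups", count data go to a chi-squared test, and "If *P* < .05, it was considered as a statistically significant difference". No order of testing, no adjustment, and no statement whether one or all primary outcomes must succeed.

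**The concern.** The protocol gives two answers to the question of which outcome decides the trial. Section 2.4 points to IL-6. The abstract and 3.2 give IL-6, TNF-α and wound pathogens equal standing. Section 3.5 then supplies a threshold that applies equally to each of them.

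Under this wording, an investigator who finds no difference in IL-6 but P < .05 for TNF-α or pathogens could report a positive primary result without departing from the protocol. Because no visit is fixed, the choice of week is open too. The 5% error rate that goes with the sample size would then not apply to the efficacy claim, and the deciding result could be picked after the data are seen.

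**Working it through.** **1. The plan's own figure.** Inputs from 2.4: means 6.14 and 6.21 (difference 0.07), a further value of 0.04 entered in the calculation, SD 0.14, alpha 0.025 (read as one-sided), power 80%, allocation 1:2. The stated 20 + 40 is reproduced when the distance is 0.07 + 0.04 = 0.11:

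- Standard error = 0.14 × √(1/20 + 1/40) = 0.0383; 0.11 / 0.0383 = 2.87.
- Power = Φ(2.87 − 1.96) = 81.8% by the normal approximation, and 80.5% by the noncentral t with 58 degrees of freedom.
- The t-based calculation returns exactly 20 and 40.

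So the whole sample size is spent on one IL-6 comparison at one-sided 0.025, which corresponds to two-sided 0.05. Nothing is reserved for a second or third primary test. (Whether adding 0.04 suits a superiority trial is a separate question and is not pursued here.)

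**2. Three outcomes, one visit, any one sufficient.** Section 3.5 does not state sidedness; two-sided 0.05 is assumed. For independent tests:

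1 − (1 − 0.05)³ = 1 − 0.857 = 14.3%.

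The protocol gives no correlation between the outcomes, so a range is shown. Simulating three correlated normal test statistics with a common correlation gives:

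| Correlation between outcomes | Chance of at least one P < .05 under no effect |
|---|---|
| 0 | 14.3% (exact) |
| 0.3 | 13.5% |
| 0.5 | 12.6% |
| 0.7 | 10.9% |
| 0.9 | 8.4% |

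The independence value is therefore an approximate maximum at one visit, not a minimum. Every value in the table is above 5%.

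**3. Benefit direction only.** The figures above count differences in either direction. If each of three independent tests is read as a one-sided test of benefit at 0.025, the rate is 1 − 0.975³ = 7.3% against 2.5%. The proportionate inflation is about the same (close to threefold) and the absolute risk about half. A chi-squared test of pathogen distribution has no direction, so this figure is only a guide.

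**4. If any week could also count.** This needs a number of weeks and a correlation between weeks, and the protocol gives neither. Assuming within-outcome correlation from 0 to 0.9 and between-outcome correlation from 0 to 0.5, simulation gives:

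| Assumed weekly tests | Range |
|---|---|
| 2 | 17% to 26% |
| 4 | 22% to 46% |
| 8 | 27% to 71% |

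The spread shows that the direction is clear and the size is not.

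**5. Power if three primaries are kept under Holm.** The first step uses two-sided 0.05/3 = 0.0167, critical value 2.394. For IL-6 with the inputs of step 1: Φ(2.87 − 2.394) = 68.3% by the normal approximation, 65.7% by the noncentral t. The planned power was about 80%.

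**The case against.** **IL-6 may already be the sole decider.** Section 2.4 does call it the main indicator, and if it alone decides at one visit the other outcomes add no inflation. That is right. But neither the abstract nor 3.2 says so; both call all three outcomes primary. What the documents show is a contradiction, not a declared rule that any one outcome wins. The inflation is conditional on that reading, and the point is stated that way.

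**Weekly testing is not in the plan.** A reader might infer from the weekly schedule that each outcome is tested every week, and attach a false-positive rate of 14% to 39% to the trial. The documents do not support that. Section 3.5 describes one before-and-after comparison within groups and a between-group test with no time point; weekly measurement is a sampling schedule. A figure of 39% requires an assumed number of weeks, an assumed correlation and weekly tests, and 14% is not a floor. What stands is that no week is fixed, so the reading is left open.

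**The model is simplified.** The simulation treats all three test statistics as normal. Pathogen distribution is categorical, and a chi-squared test with sparse categories at 20 versus 40 may not hold exactly 5%. This makes the figures approximate; it does not remove the inflation.

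**The SAP may settle it.** The analysis visit, the handling of repeated measures and the multiplicity procedure are commonly left to an SAP, and their absence from a journal article would not by itself be a finding. However, the conflict between 2.4 and 3.2 and the single threshold in 3.5 are stated in the article itself.

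**Conclusion.** The point holds in limited form. The protocol sizes the trial on IL-6 alone, lists three unranked primary outcomes, names no deciding visit, and applies one P < .05 threshold to everything. If any one of the three may carry the efficacy claim, the two-sided false-positive rate at a single visit is up to about 14% instead of 5%, or about 8% to 13.5% for positive correlation of 0.9 to 0.3. This assumes two-sided tests that each hold their nominal 5%. For a claim of benefit only, the independent-test figure is about 7.3% against 2.5%.

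The rate would be higher if any week could count, by an amount the document does not determine. If IL-6 alone decides at one fixed visit, there is no inflation from this source, but the protocol must then say so consistently.

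**What to change.** Reconcile 2.4, 3.2, 3.5 and the abstract:

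- Make IL-6 at one prespecified visit the single primary outcome, in line with the sample size. End of treatment is one example; the protocol names no visit, so the sponsor has to choose and state one before unblinding.
- Move TNF-α and wound pathogens to key secondary outcomes, tested in a stated order and only if IL-6 succeeds.
- Use the remaining weekly values descriptively or in one repeated-measures model.

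IL-6 keeps its planned alpha, so no extra patients are needed and the change is one of wording. The cost is that TNF-α and pathogens lose stand-alone primary status and cannot support a confirmatory claim if IL-6 fails.

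Keeping all three as primary under Holm at an overall two-sided 5% would also control the error rate, but it is not a wording change only. Under the inputs that reproduce 60 patients, IL-6 power at the first step falls from about 80% to about 66% to 68%. It is the less favourable option at this sample size.

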## Discussion

4

The DF is a serious public health problem in global health, which not only affects the quality of life of patients and families, but also greatly increases the financial burden on health care. DFI is an important reason for aggravating the long-term nonhealing of DF.^[31]^ The current mainstream treatment of DFI is mainly to choose sensitive antibiotics, but long-term use will make the body less sensitive or accelerate the production of drug-resistant bacteria, so more complementary therapies need to be sought. Herbal medicine foot bath has a long history of treating surgical diseases and shows the unique advantages that are different from WM, namely significant clinical efficacy and few adverse reactions. FBD is a TCM compound that has been used in DF for a long time in our hospital's endocrinology department. Due to lack of evidence on the efficacy and safety of FBD for the treatment of DFI, we need conduct a randomized, double-blind clinical trial to determine the risks and benefits of using a FBD for DFI.

As we all know, this is the 1st clinical study to treat DFI with TCM FBD. Throughout the treatment period, we closely focused on the distribution of bacterial wounds, indicators of inflammation, ulcer healing, limb function, and drug safety. We will verify that FBD can inhibit the bacterial growth of wounds through objective indicators of bacterial culture, IL-6, and TNF-α. At the same time, the overall effect of the foot bath prescription is reflected by the change in the area of the wound, the walking distance and speed, the inner diameter of the lower extremity blood vessels, the blood flow velocity, and the TCM syndrome score table. Finally, the safety evaluation was reflected by blood cell analysis, urine analysis, stool testing, liver and kidney function indicators, and so on.

However, there were plenty of limitations in our trial. On the one hand, due to the small sample size of the subjects, large-scale data are lacking to confirm the efficacy of the foot bath prescription. On the other hand, the mechanism of action of FBD is not complete, and further research is necessary. We need to observe a large sample size in future research to understand its accuracy and rationality.

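### The primary outcome of wound pathogen distribution has no favourable direction, so a chi-squared comparison of species mix cannot by itself support the conclusion that the foot bath decoction inhibits bacterial growth

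*Protocol article*

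**What the plan says.** All references are to the protocol article.

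- **Abstract, Methods:** "The primary efficacy indicators include the types of wound pathogens, interleukin 6 and tumor necrosis factor α".
- **Outcome measures (3.2):** the second primary item is "Wound pathogen distribution: Collect samples of ulcers and use a fully automatic microbiologic tester for bacterial detection once a week". It lists no categories and does not say which result would favour treatment.
- **Statistical analysis (3.5):** "Chi-squared test was used to analyze the count data". The pathogen outcome is not mentioned by name. Fisher's exact method appears only for adverse events. The threshold is "If *P* < .05, it was considered as a statistically significant difference".
- **Discussion (4):** "We will verify that FBD can inhibit the bacterial growth of wounds through objective indicators of bacterial culture, IL-6, and TNF-α".
- **Sample size (2.4):** "This study is a superiority clinical trial with interleukin 6 (IL-6) as the main efficacy indicator". Nothing is sized for the culture outcome.

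**The concern.** The outcome as named and the conclusion to be drawn from it do not match. Both wordings of the outcome describe a category of organism. Inhibition of growth is a statement about less bacteria: clearance, lower load, or a baseline organism no longer found. A chi-squared test on a table of species asks only whether the mix differs between arms. It does not ask whether one arm has fewer infected wounds.

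At stake is a declared primary outcome. It could be reported as positive when FBD has cleared nothing, or as negative when FBD has cleared many wounds. Either result would then feed the claim that the Discussion says will be verified.

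**Working it through.** **Inputs from the article:** 20 FBD and 40 control patients (Sample size); weekly culture (Outcome measures); chi-squared for counts and P < .05 (Statistical analysis).

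**Assumed, because the article gives no figure:** the species tables, culture-negative rates, number of swabs per patient and within-patient correlation.

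**1. The plan's own figure.** The only sample-size figure is for IL-6. With n = (1.96 + 0.8416)² × 0.14² × (1 + 1/2) / d², the numerator is 7.849 × 0.0196 × 1.5 = 0.2308. Setting d = 0.07 + 0.04 = 0.11 gives 0.2308 / 0.0121 = 19.07, so 20 and 40, as stated. (With d = 0.07 alone it would be 48 and 96. How the 0.04 enters is a separate matter.) Nothing in this calculation concerns cultures.

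**2. Significant without benefit.** Suppose every patient is still culture-positive.

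| | Species A | Species B | Species C | Total |
|---|---|---|---|---|
| FBD | 12 | 4 | 4 | 20 |
| Control | 10 | 15 | 15 | 40 |

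- Expected for FBD: 20 × 22/60 = 7.33, then 20 × 19/60 = 6.33 twice. Expected for control: 14.67, 12.67, 12.67.
- χ² = 4.667²/7.333 + 4.667²/14.667 + 2 × 2.333²/6.333 + 2 × 2.333²/12.667 = 2.970 + 1.485 + 1.719 + 0.860 = 7.03.
- On 2 degrees of freedom, P = exp(−7.03/2) = 0.030.
- Swapping the labels of A and B (4/12/4 versus 15/10/15) gives the same P. The test does not know which species matters.

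**3. Null despite clearance.** Suppose 10 of 20 FBD patients and 40 of 40 controls are positive, and the isolates are 5/3/2 versus 20/12/8.

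- Expected for FBD: 10 × 25/50 = 5, 10 × 15/50 = 3, 10 × 10/50 = 2. These equal the observed counts, so χ² = 0 and P = 1.
- The same patients classed as positive or negative give, by Fisher's exact test, P = C(20,10)/C(60,10) = 184,756 / 75,394,027,566, about 0.000002.

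**4. Repeated swabs, only if pooled.** If all weekly swabs were entered as independent, the variance would be understated by the design effect 1 + (W − 1) × ICC, where W is swabs per patient. For a positive/negative split the true error of a nominal 5% test is then about 2 × [1 − Φ(1.96/√(design effect))].

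- W = 2, ICC 0.3: design effect 1.3, error 8.6% (simulated 8.2%).
- W = 4, ICC 0.5: design effect 2.5, error 21.5% (simulated 21.5%).
- A five-category table under the same two settings gave 12% and 44% in simulation.
- With one swab per patient, simulated error stayed at about 5% to 6%.

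**5. Power of a directional outcome.** Normal approximation, two-sided 0.05, 20 versus 40, control rate of culture-negativity assumed to be 30%. For 50% on FBD the pooled rate is (10 + 12)/60 = 0.367, so:

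- null SE = √(0.2322 × 0.075) = 0.132;
- alternative SE = √(0.25/20 + 0.21/40) = 0.133;
- power = Φ[(0.20 − 1.96 × 0.132)/0.133] = 33%.

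The same formula gives 61% for 60% on FBD and 86% for 70%.

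**The case against.** Several points can be made for the plan, and some of them stand.

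- **Culture is not used alone.** The Discussion relies on culture alongside IL-6 and TNF-α, and IL-6 drives the sample size. This stands. The limit is on what the species comparison contributes, not on everything the trial could show.
- **Detection might be what is counted.** Outcome measures does speak of detecting bacteria. A two-by-two comparison of detected versus not detected, with its proportions, would show direction. But the outcome is named as a distribution, and the abstract names types. Neither says detected or not detected.
- **An article condenses.** The week, the unit of analysis and the category list may sit in a fuller document, and their absence is no fault here. The mismatch between a nominal primary outcome and a directional conclusion is in the printed text.

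A reader might also infer two stronger faults that the article does not support.

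- **That repeated swabs are treated as independent.** Weekly sampling next to an unqualified chi-squared test invites this reading. Statistical analysis states neither the unit nor the week, so pooling is an inference.
- **That sparse cells invalidate the test.** Five equally common species would give an expected count of 20 × 0.20 = 4 per cell in the FBD arm, but no species list is given. Under that scenario, 40,000 simulated null trials with one culture per patient rejected in 4.8%. Skewed mixes of five and seven species gave 4.6% and 3.9%. False positives are not inflated.

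**Conclusion.** The point holds in a limited form. The pathogen outcome is nominal and the stated test for counts has no direction. A species-mix comparison therefore cannot by itself support the conclusion that FBD inhibits bacterial growth. This follows from the text and needs no assumed figure; the example tables only show that it can fail both ways (P = 0.030 with no clearance, P = 1 with half the FBD arm cleared).

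It would go too far to say that the trial cannot show inhibition at all, or that the plan has an inflated false-positive rate. The rise from 5% to about 8% to 21% applies only if swabs were pooled as independent, with an assumed 2 to 4 swabs per patient, within-patient correlation of 0.3 to 0.5 and a positive/negative split.

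**What to change.** Define one directional outcome per patient, at a named time, from the weekly cultures already planned. Examples are culture-negative, or baseline pathogen no longer detected, at end of treatment, among patients with a positive baseline culture. Compare the arms by Fisher's exact test and report the risk difference with a 95% CI. Report species distribution descriptively. If all weekly cultures are to be analysed, use a model that clusters on the patient (GEE or mixed). State that the first culture is taken before treatment: Outcome measures says so for the cytokines but gives only a frequency for cultures.

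**Cost.** No new sampling schedule is needed, but this is more than a change of wording. It redefines a primary outcome of a registered trial, and Ethics and dissemination (2.2) requires renewed ethics committee consent for amendments; the registry entry must follow. Patients with a negative baseline culture drop out of this outcome, and Eligibility criteria (2.8) does not require a positive one. The powers of 33% and 61% are therefore upper limits: they use all 60 patients and a normal approximation, and Fisher's test is more conservative. The estimate and its interval should carry the interpretation more than the P value.
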